### 2.10. Compliance and Discontinuation

Based on our previous pilot study [8], we concluded that if the study participants receive six to eight acupuncture sessions in compliance with the regulations, this will be sufficient to generate valid and reliable data. For participants who drop out before their sixth acupuncture session, data from the last visit will be used for analysis. The research coordinator will regularly encourage participants to continue to the end of the trial.

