### 2.11. Outcome Measures

The study outcomes will be evaluated by an investigator blinded to the treatment assignments. There will be no separation between primary and secondary outcomes since the aim of this study is not to confirm the effectiveness of acupuncture treatment in patients with AD but to discover the response determinants and the mechanism of action of acupuncture treatment for AD, mainly focusing on the gut-brain axis.

Clinical outcomes can be divided into three categories: First, we will assess (1) symptoms of AD (changes in SCARAD, EASI, and Dermatology Life Quality Index [DLQI] assessments). We will also assess (2) GI symptoms (changes in abdominal examination findings, as well as changes in scores according to the Gastrointestinal Symptom Rating Scale (GSRS), Total Dyspepsia Symptom (TDS) scale, Bristol Stool Form Scale (BSFS), and the adequate relief of functional dyspepsia pain and discomfort (AR) assessment). These values will be measured at week 0 (baseline), week 2 (midterm), and week 4 (endpoint).

Finally, since this study aims to explore the mechanism of acupuncture, we will also investigate (3) gut-brain axis indicators. First, the changes in the intensity of blood-oxygen level-dependent (BOLD) signals in the pain and itch matrix, including the thalamus, insula, and cingulate cortex, will be measured using fMRI. Additionally, the functional connectivity between the pain and itch matrix regions will be analyzed. Second, a fecal sample will be taken, and the composition of the gut microbiota in the feces will be analyzed. Blood samples will also be collected and analyzed for TARC and ATX in the serum.

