#### 2.12.1. Statistical Analysis for AD Symptom and GI Symptom Assessments

The continuous variables, including SCORAD, EASI, DLQI, GSRS, and TDS scores, will be presented as mean ± standard deviations with 95% confidence intervals. In the analysis, if the result values follow the mean distribution, the independent two-sample *t-*test can be used; otherwise, the Mann–Whitney *U* test can be used.

On the other hand, the abdominal examination, BSFS, and AR variables are categorical. These will be expressed as *n* (%), and as mentioned above, these will be analyzed using the chi-square test or Fisher's exact test. Data from the 40 participants in the VA group will be compared with those of the 20 participants in the SA group.

For the 40 participants in the VA group, additional analyses will be conducted. With the primary endpoint being the total SCORAD score, we will first analyze the correlation as a continuous variable through regression analysis. The dependent variables will include GSRS, TDS, BSFS, and AR values, as well as abdominal examination findings, which are indicators of GI symptoms.

In addition, based on the above data, we will explore the cutoff total SCORAD value that can distinguish between high and low responders. The reference value set through this process will be divided into categorical variables to evaluate the association with GI symptoms again. The minimal clinically important difference (MCID) acts as an important cutoff that determines whether a response is clinically useful, meaning 8.7 points in total SCORAD and 8.2 points in objective SCORAD [24]. The MCID value will be used for analysis as a reference cutoff value. The purpose of this study is to identify factors associated with response determination by performing a correlation analysis with the above method.

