#### 2.12.2. Statistical Analysis for Gut-Brain Axis Indicators

Changes in the gut-brain axis indicators before and after acupuncture will be analyzed within and between groups.

*(1) Gut Microbiota Analysis*. The significance of categorical variables will be determined using the nonparametric Mann–Whitney test for two category comparisons or the Kruskal–Wallis test when comparing three or more categories. Multivariate analyses of variance (PERMANOVA, 999 permutations) with the vegan function Adonis will be performed to test whether community composition is significantly different according to the features associated with sequencing data.

*(2) Serum TARC, ATX Analyzing*. The significance of continuous variables will be determined using the independent two-sample *t*-test or the Mann–Whitney *U* test. The variables will be presented as mean ± standard deviation with 95% confidence intervals.

*(3) fMRI Analysis*. (i) Preevaluation for fMRI session: the between-group and AD severity-dependent differences in interoceptive and exteroceptive properties will be analyzed using mixed-model linear regression and analysis of variance (ANOVA), with the subject as a random factor. Interoceptive and exteroceptive outcomes will be correlated with functional brain activities (voxel-wise beta-series from sensory imagination tasks) and subjective itch and pain ratings of the tasks, which will be performed during fMRI scanning using Pearson's correlation analyses with and without covariates (AD severity, group). If nonparametric data in one or both variables were present, Spearman's rank order correlation will be used. (ii) fMRI data: raw fMRI data will be preprocessed with Analysis of Functional NeuroImages (AFNI, https://afni.nimh.nih.gov) including slice time correction, alignment, registration, masking, smoothing using a Gaussian kernel, and scaling. For the resting-state fMRI signals, the seed-based amplitude of low-frequency fluctuations, functional connectivity, and graph theory analyses will be performed. Task-related BOLD signals will be compared as a function of the four different types of imagination tasks described below using general linear model tests.

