## Figures and Tables

**Figure 1 fig1:**
[figure not shown]
Study flowchart. The light-yellow area depicts the randomized controlled trial component, and the dark-yellow area depicts the cross-sectional component.

**Table 1 tab1:** Study schedule for the AD patient group.

Outcome values and intervention		Baseline assessment	Treatment period								Final assessment
			1-week		2-week		3-week		4-week		
AD symptoms	SCORAD assessment	●				●					●
	EASI assessment	●				●					●
	DLQI assessment	●				●					●

GI symptoms	Abdominal examination	●				●					●
	GSRS assessment	●				●					●
	TDS assessment	●				●					●
	Bristol stool scale	●				●					●
	AR assessment			●	●	●	●	●	●	●	●

Gut-brain axis	BDI STAI-X1, 2	●									
	fMRI image (tasks 1 and 3)	●									●
	Stool collection	●									●
	Blood collection	●									●

	Acupuncture treatment		●	●	●	●	●	●	●	●	

	Investigate for adverse events		●	●	●	●	●	●	●	●	●

BDI, Beck Depression Inventory; STAI, State-Trait Anxiety Inventory; SCORAD, Scoring Atopic Dermatitis; VAS, Visual Analog Scale; EASI, Eczema Area and Severity Index; DLQI, Dermatology Life Quality Index; GSRS, Gastrointestinal Symptom Rating Scale; TDS, Total Dyspepsia Symptom Scale; AR, adequate relief of functional dyspepsia pain and discomfort; AD, atopic dermatitis. Except for the fMRI session, the baseline assessment will take between 30 minutes and 1 hour. An fMRI session, performed at the first and last evaluations, will take about an hour and a half to two hours. Each acupuncture session will take about 15 to 20 minutes. And a total of 30 to 45 minutes will be required for the questionnaires administered in the intermediate and final evaluations. Visit window is ±5 days. Baseline assessment—first acupuncture treatment and eighth acupuncture treatment—Endpoint assessment will be performed within 7 days. The visit window period is ±5 days.

**Table 2 tab2:** Study schedule for the healthy controls.

	Measurements	Assessment	Optional assessment (*n* = 25)
Gut-brain axis	BDI STAI-X1,2	●	
	fMRI image (tasks 1 and 3)	●	
	fMRI image (task 2, *n* = 25)		●
	Stool collection	●	
	Blood collection	●	

BDI, Beck Depression Inventory; STAI, State-Trait Anxiety Inventory. Except for the fMRI session, the baseline assessment will take between 30 minutes and 1 hour. An fMRI session will take about an hour and a half to two hours.

**Table 3 tab3:** Revised STRICTA checklist.

Item	Detail

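### The carry-forward rule for dropouts before session six forces zero change in gut-brain measures, and in most clinical scores for those who leave before session four

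*Protocol article*

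**What the plan says.** Section 2.10 (Compliance and Discontinuation) regards six to eight of the eight sessions as adequate exposure: "if the study participants receive six to eight acupuncture sessions in compliance with the regulations, this will be sufficient to generate valid and reliable data". It then fixes the handling of anyone who leaves earlier: "For participants who drop out before their sixth acupuncture session, data from the last visit will be used for analysis". It names no outcomes and no exceptions.

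For the AD and GI scores, section 2.11 states: "These values will be measured at week 0 (baseline), week 2 (midterm), and week 4 (endpoint". Table 1 puts the midterm mark in the fourth of eight treatment columns. Its footnote says of imaging: "An fMRI session, performed at the first and last evaluations, will take about an hour and a half to two hours". The rows "Stool collection" and "Blood collection" each carry two marks, baseline and final. AR has no baseline mark and is asked from the second session onward. No early-termination assessment appears.

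Two analyses use these values. Section 2.12.2 says: "Changes in the gut-brain axis indicators before and after acupuncture will be analyzed within and between groups". Section 2.12.1 looks for a cutoff separating high from low responders in the VA arm and takes the minimal clinically important difference as reference, "meaning 8.7 points in total SCORAD and 8.2 points in objective SCORAD".

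**The concern.** Read plainly, the rule is last observation carried forward. That method is only as good as the last observation, and here the schedule is sparse. For many of the people and outcomes covered, the last observation is the baseline itself, so the imputed treatment response is zero by arithmetic and not by measurement.

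The stated main purpose is to find what determines response to acupuncture. If people who left early enter the low-responder group because they left, the analysis partly finds predictors of leaving. The same zeros pull each arm's mean change toward zero in proportion to its own dropout, so the VA-SA difference can move in either direction.

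**Working it through.** **Inputs.** From the documents: the rule (section 2.10), which covers people whose last attended session is 0 to 5; the marks in Table 1; the 8.7-point reference cutoff (section 2.12.1); 40 VA and 20 SA participants (section 2.2.3). Assumed, because the documents give neither: dropout rates of 5% to 20%, and true SCORAD improvements of 12 (VA) and 5 (SA). The plan has no figure of its own on this point to reproduce.

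**Step 1: what gets carried forward.**

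| Last session attended | SCORAD, EASI, DLQI, abdominal examination, GSRS, TDS, BSFS | fMRI, stool, serum |
|---|---|---|
| 0 to 3 | baseline, change = 0 | baseline, change = 0 |
| 4 or 5 | week-2 value stands in for week 4 | baseline, change = 0 |

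This step needs no assumption beyond reading the rule as carry-forward.

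**Step 2: VA-SA difference.** If a fraction dV of VA and dS of SA leave before session 4, the expected difference is (1 − dV) × 12 − (1 − dS) × 5. The true difference is 12 − 5 = 7.

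- 15% and 15%: 10.2 − 4.25 = 5.95 (−15%)
- 20% VA, 10% SA: 9.6 − 4.5 = 5.1 (−27%)
- 5% VA, 15% SA: 11.4 − 4.25 = 7.15 (+2%)

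If both arms truly improve by 8.7 points and dropout is 10% in VA and 20% in SA, a difference appears where none exists: 8.7 × (0.20 − 0.10) = 0.87 points.

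**Step 3: responder label.** A change of 0 is below 8.7, and below any positive cutoff. Suppose 4 of 40 VA participants leave before session 4 and 16 others are genuine low responders. Then 4 of the 20 labelled low responders (20%) are people whose response was never observed.

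**Step 4: correlation, only if GI is analysed as change.** Take two change scores, uncorrelated in completers, each with SD 1 and means m1 and m2, with a fraction p set to zero on both. The induced correlation is p(1 − p)·m1·m2 / √(v1·v2), where v = (1 − p) + p(1 − p)m². At p = 0.15:

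- m1 = m2 = 1: 0.1275 / 0.9775 = 0.13
- m1 = 1.5, m2 = 1: 0.19125 / √(1.1369 × 0.9775) = 0.18

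**Step 5: precision and power.** With the same v and p, the standard error of the VA mean change after carry-forward is √(v/40), against √(1/34) = 0.171 on observed cases. At m = 1 it is √(0.9775/40) = 0.156; at m = 1.5 it is √(1.137/40) = 0.169. The understatement is therefore about 2% to 9%.

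For power, take a standardised effect of 0.767 (80% power at 40/20, two-sided 0.05, no dropout) and set a fraction d to zero in each arm. Power = Φ((1 − d) × 0.767/SE − 1.96), with SE² = sV²/40 + sS²/20, sV² = (1 − d)(1 + 0.767²) − ((1 − d) × 0.767)² and sS² = 1 − d. This gives 74.9% at d = 10%, against 75.7% on observed cases, and 69.1% against 70.7% at d = 20%. The harm is bias and mislabelling, not lost power.

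**The case against.** The strongest reply has four parts.

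- **The trial is not confirmatory.** Sections 2.2.3 and 2.11 say it does not set out to confirm effectiveness, so bias in the VA-SA difference matters less than in an efficacy trial. That stands. It does not protect the determinant analysis, which is the exploratory question itself.

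- **The sentence never names last observation carried forward.** It might mean that where the last visit yielded no scan or sample there is nothing to use, or that a withdrawal assessment was intended. The first reading is possible for fMRI, stool and serum, but the sentence restricts nothing. The second has no support in Table 1. Either way the text needs rewording.

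- **The size is unknown.** No dropout rate or effect size is given, and one of the three illustrations moves the difference by only 2%. That stands.

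- **The artificial correlation needs change scores on both sides.** Section 2.12.1 lists GI values, and the Discussion speaks of presence or absence of GI symptoms, which could be baseline status. Section 2.11 does speak of GI changes. The point is therefore conditional.

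A reader might also infer that every VA dropout becomes a low responder, or that all fMRI, stool and serum results are compromised. The documents support neither. Someone leaving after session 4 or 5 carries a genuine week-2 SCORAD, which may exceed 8.7. The zeros affect only before-after change in dropouts the rule covers; completers and the baseline comparison with healthy controls are untouched. AR has no baseline, so carrying it forward forces no zero.

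**Conclusion.** The point holds with these limits. As written, the rule sets clinical change to zero for participants who leave before the session-4 assessment and before-after gut-brain change to zero for all who leave before session 6. It substitutes week 2 for week 4 in those who leave after session 4 or 5. VA participants who leave before session 4 become low responders by construction, in the analysis that carries the trial's main aim.

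The mechanism follows from section 2.10 and Table 1 alone. The magnitudes do not: they rest on assumed improvements of 12 and 5 points, assumed dropout, and all dropout falling before session 4. On those assumptions a difference of 7 becomes 5.95 or 5.1, or is barely changed, depending on how dropout splits between arms. The effects on standard error and power are minor and are not the reason to act.

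**What to change.** Replace the carry-forward sentence in section 2.10 before unblinded analysis:

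- **Repeated clinical scores:** use all observed week-2 and week-4 data in a likelihood-based repeated-measures model with arm, time, their interaction and baseline as covariate.
- **fMRI, stool and serum:** analyse change on observed baseline-final pairs only; never impute zero change.
- **Responder and determinant analysis:** treat VA participants with no post-baseline SCORAD as missing, not as low responders, and report a sensitivity analysis of that choice.
- **Data collection:** where feasible, invite people who stop sessions to the final assessment already in the schedule.

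The first three are changes of wording. The fourth costs some extra visits, and a final fMRI session takes one and a half to two hours, so partial attendance (scores only) may be all that is feasible. The downsides are slightly fewer participants in the change and responder analyses and reliance on a missing-at-random assumption. A participant with neither a week-2 nor a week-4 score contributes nothing to a model with baseline as covariate. The repeated-measures model is one sound option; the essential change is that a baseline value no longer stands in for an outcome.

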### 2.11. Outcome Measures

The study outcomes will be evaluated by an investigator blinded to the treatment assignments. There will be no separation between primary and secondary outcomes since the aim of this study is not to confirm the effectiveness of acupuncture treatment in patients with AD but to discover the response determinants and the mechanism of action of acupuncture treatment for AD, mainly focusing on the gut-brain axis.

Clinical outcomes can be divided into three categories: First, we will assess (1) symptoms of AD (changes in SCARAD, EASI, and Dermatology Life Quality Index [DLQI] assessments). We will also assess (2) GI symptoms (changes in abdominal examination findings, as well as changes in scores according to the Gastrointestinal Symptom Rating Scale (GSRS), Total Dyspepsia Symptom (TDS) scale, Bristol Stool Form Scale (BSFS), and the adequate relief of functional dyspepsia pain and discomfort (AR) assessment). These values will be measured at week 0 (baseline), week 2 (midterm), and week 4 (endpoint).

Finally, since this study aims to explore the mechanism of acupuncture, we will also investigate (3) gut-brain axis indicators. First, the changes in the intensity of blood-oxygen level-dependent (BOLD) signals in the pain and itch matrix, including the thalamus, insula, and cingulate cortex, will be measured using fMRI. Additionally, the functional connectivity between the pain and itch matrix regions will be analyzed. Second, a fecal sample will be taken, and the composition of the gut microbiota in the feces will be analyzed. Blood samples will also be collected and analyzed for TARC and ATX in the serum.

#### 2.11.1. AD Symptom Assessments

*(1) Scoring Atopic Dermatitis (SCORAD)*. The SCORAD score was developed by the European Task Force on Atopic Dermatitis (ETFAD) as a tool to assess the severity of AD [13]. It evaluates not only objective signs but also subjective symptoms, such as itching and insomnia.

*(2) Eczema Area and Severity Index (EASI)*. The EASI is considered a complementary evaluation tool to the SCORAD scale because it more specifically evaluates symptoms of acute and chronic inflammation [14].

*(3) Dermatology Life Quality Index (DLQI)*. The DLQI is a tool for evaluating the quality of life, and it can evaluate psychological distress caused by skin symptoms [15]

#### 2.11.2. GI Symptom Assessments

*(1) Abdominal Examination*. Abdominal examination is a commonly used diagnostic method in Korean medicine. Abdominal examination in Korean medicine differs from the physical abdominal examination of Western medicine because the Korean variation follows the Korean medical theory that specific responses appear at the body surface (abdomen) when the disease exists inside the human body. Therefore, in this study, we will use abdominal examination to detect GI symptoms [16]. Specific details include evaluation of tenderness in CV12 and ST25 on both sides and confirmation of the presence of stuffiness below the heart (*Simhabi, 心下痞*) and stuffiness and rigidity below the heart (*Simhabikyung,* 心下痞硬). Both *Simhabi* and *Simhabikyung* are symptoms that occur in the anticardium (the area encompassing CV13 and CV14). The former, *Simhabi*, includes the patient's feeling of fullness, bloating, stuffiness, and blockage in the epigastric region, which is felt only subjectively, but there is no objective resistance or tenderness. It includes all kinds of stomach upset, epigastric fullness after meals or as usual. *Simhabikyung* refers to a case in which a doctor can sense resistance in the epigastric region objectively by hand [17, 18].

*(2) Gastrointestinal Symptom Rating Scale (GSRS)*. The GSRS can be used to evaluate both upper and lower GI symptoms. In addition to pain, soreness, and indigestion affecting the upper GI tract, the characteristics of the stool and discomfort can also be evaluated together [19].

*(3) Total Dyspepsia Symptom Scale (TDS)*. The TDS is a tool used primarily for evaluating symptoms in patients with functional dyspepsia, particularly postprandial bloating, premature satiety, nausea, vomiting, and belching [20].

*(4) Bristol Stool Form Scale (BSFS)*. The BSFS is a proper tool in daily clinical practice. It is a quick, easy, and intuitive patient-reported measure of whole-gut transit time, and it can be used as a substitute for stool consistency [21].

*(5) Adequate Relief of Functional Dyspepsia Pain and Discomfort (AR)*. The content is as follows: “Have you experienced appropriate relief (more than 50% reduction) of the pain or discomfort associated with your dyspepsia after the last acupuncture treatment?” AR asks about the degree of improvement in general and nonspecific digestive discomfort [7].

#### 2.11.3. Gut-Brain Axis Indicators

*(1) Fecal Sampling and Microbiota Analysis Protocol*. For each participant, approximately 200 mg of fecal samples will be employed as an input for DNA extraction with the FastDNA for the fecal kit (MP Bio, Santa Anna, CA, USA) following the manufacturer's instructions. The V3-V4 hypervariable regions of the 16S rRNA gene will be targeted using a universal primer set (5ʹ-CCTACGGGNGGCWGCAG and 5ʹ-GACTACHVGGGTATCTAATCC) with sequencing barcodes. Sequencing will be performed on an Illumina MiSeq platform with 2 × 250 bp paired-end protocol yielding pair-end reads. We mainly follow the QIIME2 pipeline [8] for bacteria profiling based on 16S rRNA. DADA2 will be selected as a tool for sequence quality control, and the EzTaxon [9] database will be chosen as the taxonomic reference database. The results will be imported into the *R* statistical environment (The *R* Foundation, https://cran.r-project.org/) for further analysis using the Bioconductor package phyloseq [10]. Alpha-diversity will be determined by the value of clustered observed operation taxonomic units (OTUs), Shannon index, and the inverse Simpson index. Beta diversity will be assessed using weighted or unweighted UniFrac distance matrices.

*(2) Blood Sampling and Analysis of TARC and ATX*. Blood samples will be collected in the blood collection room on the second floor of Kyung Hee Medical Center. After clotting, the serum will be separated by centrifugation at 3000 rpm for 10 minutes and stored at −80°C. Analysis of TARC and ATX will be conducted using commercial ELISA kits at the AMSRC.

*(3) fMRI*. (i) Preevaluation for fMRI sessions: interoceptive and exteroceptive properties for each individual will be measured before the fMRI sessions; (ii) fMRI session: (a) fMRI data acquisition—fMRI data on a 3 T MRI scanner (Siemens, Erlangen, Germany) with a three-axis gradient head coil will be acquired. Anatomical images using a T1-weighted rapid gradient-echo sequence with TR = 2000 ms, TE = 2.37 ms, a flip angle of 9°, a field of view of 240 × 240 mm^2^, and a slice thickness of 1.0 mm will be acquired. Resting-state and task-related functional images will be acquired with a T2∗-weighted gradient-echoplanar imaging sequence (37 slices; TR = 2000 ms; TE = 30 ms; flip angle, 90°; field of view, 240 × 240 mm^2^; slice thickness, 4.0 mm; voxel size = 3.8 mm 3.8 mm × 4 mm^3^). (b) Video watching and sensory imagination tasks—the stimulus materials consist of various types of videos, which were recorded by the researchers, belonging to four categories: images showing painful events (pain condition; acupuncture needle rotation, hammer hitting fingers, knife cutting skin, pinprick pricking face, etc.), images evoking itch (itch condition; scratching neck, arm, leg, chest, and abdomen), images showing nonpainful events (control condition for pain condition; depictions of cotton, pen, straw, brush on hand, arm, and face), and images evoking nonitch rest (control condition for itch condition; tapping neck, arm, leg, chest, and abdomen). Pain and nonpain videos, itch and nonitch videos were matched each other in terms of velocity of the motion, body part, model, background, and context. Items for pain, nonpain, itch, and nonitch videos were used in previous pain imaginary task studies [22] and contagious itch studies [23]. Itch and nonitch videos will depict female or male researchers performing scratching or tapping behavior without revealing their faces, female participants will watch videos recorded with female researchers, and male participants will watch videos recorded with male researchers. Participants will be asked to imagine that the stimuli (painful or nonpainful) and behaviors (scratching or tapping) shown in the videos are happening to them while watching the videos. Each video will continue for 2 seconds, and each trial will consist of four consequent videos of the same category. The order of trials will be pseudorandomized without repetition of two consecutive categories. In each block, 24 trials (six trials per condition) will be presented with a randomly generated interstimulus interval (minimum interval, 10 seconds; maximum interval, 20 seconds; mean of intervals, 15 seconds). All participants will complete an fMRI session consisting of five blocks, and they will have as much rest as they request between each block. After each block, participants will rate verbally how much they experience itch and pain sensations while watching the videos (0: not painful/itchy at all, 10: very much painful/itchy). In total, the duration of the fMRI scan will be approximately 60 minutes for all participants.
